### Reporting SAEs

Each principal investigator (PI) must record all AEs and report SAEs in English to the Clinical trial Coordinating centre (CTCC) in Cambridge, using the trial-specific SAE form, within 24 hours of their awareness of the event; the sponsor must then immediately forward the form to Sanofi. The co-ordinating centre will perform an initial check of the report, request any additional information, and will pass it on to the chief investigator (CI) or nominated clinician without delay.

The CI is responsible for the onward notification of all SAEs to the sponsor immediately but not more than 24 hours of first notification. A detailed record of all SAE’s reported to the sponsor will be kept. The CI is also responsible for prompt reporting of all SAE findings to the competent authority if they could: (1) adversely affect the health of participants, (2) impact on the conduct of the trial, (3) alter the risk to benefit ratio of the trial, (4) alter the competent authority’s authorisation to continue the trial in accordance with Directive 2001/20/EC. PIs will be informed of all suspected unexpected serious adverse reactions (SUSARs) and will ensure it is reported to their relevant authorities in accordance with their own regulations.

SAEs will also be reported to the IMP manufacturer in accordance with the pharmacovigilance agreement and be reviewed at the next IDMC meeting.

### Reporting of suspected unexpected serious adverse reactions

All suspected ARs related to an IMP (the tested IMP and comparators) which occur in the concerned trial, and that are both unexpected and serious (SUSARs) are subject to expedited reporting. Each PI must notify all SUSARs, in English, to the CTCC in Cambridge, using the trial-specific SAE form, immediately as they become aware of the event.

The CI must report all the relevant safety information previously described, to the: (1) sponsor, (2) competent authorities in the concerned member states, (3) Ethics Committee in the concerned member states and (4) IMP manufacturer. The CI shall inform all investigators concerned of relevant information about SUSARs that could adversely affect the safety of participants.

For fatal or life-threatening SUSARs, all parties listed in the paragraph above must be notified as soon as possible but no later than seven calendar days after the trial team and sponsor has first knowledge of the minimum criteria for expedited reporting. In each case, relevant follow-up information should be sought and a report completed as soon as possible. It should be communicated to all parties within an additional eight calendar days. Non-fatal and non-life-threatening SUSARs must be reported as soon as possible but no later than 15 calendar days after first knowledge of the minimum criteria for expedited reporting. Further relevant follow-up information should be given as soon as possible.

Information on the final description and evaluation of an AR report may not be available within the required time frames for reporting. For regulatory purposes, initial expedited reports of SUSARs should be submitted within the time limits as soon as the minimum following criteria are met: (1) a suspected IMP, (2) an identifiable participant (eg, trial participant code number), (3) an AE assessed as serious and unexpected, and for which there is a reasonable suspected causal relationship, (4) an identifiable reporting source and (5) when available and applicable a unique clinical trial identification (EudraCT number) and a unique case identification (ie, sponsor’s case identification number). In case of incomplete information at the time of initial reporting, all the appropriate information for an adequate analysis of causality should be actively sought from the reporter or other available sources. Further available relevant information should be reported as follow-up reports. In certain cases, it may be appropriate to conduct follow-up of the long-term outcome of a particular reaction. Electronic reporting is the expected method for expedited reporting of SUSARs to the competent authority. The format and content as defined by the competent authority should be adhered to. SUSARs will be reported in English to the IMP manufacturer in the format as described in the agreement.

### Pregnancy reporting

Pregnancy occurring from written informed consent/assent until the end of the trial period, that is, 12 months following the end of the treatment period should be reported and followed up until the outcome of the pregnancy is known. All pregnancies within the trial (either the trial participant or the participant’s partner) should be reported to the CI and the sponsor and IMP manufacturer using the relevant Pregnancy Reporting Form within 24 hours of notification. Pregnancy is not considered an AE unless a negative or consequential outcome is recorded for the mother or child/fetus. If the outcome meets the serious criteria, this would be considered an SAE.

### Toxicity management

All dose interruptions/reductions, and the reasons for the interruptions/reductions, are to be recorded in the eCRF. Medications given to manage toxicities are also to be recorded in the eCRF. In the event of toxicity reactions (hypersensitivity, allergic reaction, serum sickness and haematological effects) during the trial treatment infusion, the guidance in the below sections may be followed regarding dose interruptions and discontinuation. Any rescue medication required administered should be in line with advice given to local investigators and in appropriate facilities. In the event of toxicity reactions after the end of trial treatment infusion, any rescue medication required should be administered in line with local procedures.

CRS is caused by a large, rapid release of cytokines into the blood from immune cells affected by immunotherapy. Signs and symptoms of CRS include fever, nausea, headache, rash, rapid heartbeat, low blood pressure and breathing difficulties. Most participants are expected to have a mild reaction, but sometimes, the reaction may be severe or life threatening. Participants may experience CRS following ATG/placebo infusion. If CRS severity is mild (grade 1) then the trial treatment can be continued. If the CRS severity is moderate (grade 2) then the trial treatment may be interrupted and restarted once signs and symptoms improve. If a subsequent dose of ATG/placebo further exacerbates the signs and symptoms of CRS despite following the guidelines in the MELD-ATG Trial Manual, the treatment must be permanently discontinued, and additional supportive/resuscitative measures given as clinically indicated. However, if CRS severity is severe (≥grade 3), then trial treatment should be permanently discontinued.

In rare cases, participants may experience hypersensitivity, which refers to immediate allergic, IgE-mediated reactions to ATG. Such participants primarily develop skin rash and respiratory distress early in the course of the infusion (usually within the first hour). For such reactions, the infusion should be discontinued, and the participant managed according to local hospital procedures.

Other allergic reactions to trial treatment infusion may be managed based on the severity of the allergic reaction. A mild (≤grade 1–2) allergic reaction will allow trial medication to be restarted at the discretion of the investigator. With either a severe (grade 3) reaction or a life-threatening (grade 4) allergic reaction, trial medication should be permanently discontinued. In case of anaphylaxis (begins at CTCAE grade 3 or higher), the trial treatment infusion should be terminated immediately, and appropriate emergency treatment should be initiated. Equipment for emergency therapy for anaphylactic shock must be readily available.

Serum sickness from host immunisation against rabbit protein may occur 7–15 days after the first dose of ATG. It is a reaction that is similar to an allergy. Signs and symptoms can take as long as 14 days after exposure to appear, and may include signs and symptoms commonly associated with hypersensitivity or infections including rashes, itching, arthralgia (especially finger and toe joints), fever (as high as 40°C and usually appears before rash), lymphadenopathy (particularly near the site of injection, head and neck), malaise, hypotension, splenomegaly, glomerulonephritis, protein or blood in the urine or shock. The participants than may require glucocorticoid treatment for supportive care. The dose will depend on the severity of signs and symptoms and guidance is provided in the MELD-ATG Trial Manual. The least amount of steroid required to provide symptomatic relief of serum sickness, due to the effect of glucocorticoid on blood glucose.

Haematological effects such as thrombocytopaenia and/or leucopaenia (including lymphopaenia and neutropaenia) may occur and are reversible. FBC will be reviewed following completion of the first ATG/placebo infusion. A 50% dose reduction is permissible for the second ATG/placebo infusion if required as per the SmPC^22^ if the platelet count is between 50 and 75 x10ˆ9/L (50 000 and 75 000 cells/mm^3^) or if the white cell count (WCC) is between 2 and 3 x10ˆ9/L (2000 and 3000 cells/mm^3^). Before this happens, the FBC will first be repeated and if the platelet count is over 75 x10ˆ9/L (75 000 cells/mm^3^) on repeat or if the WCC is over 3 x10ˆ9/L (3000 cells/mm^3^), then the second ATG or placebo infusion will be given as planned. If on repeat FBC, the platelet count is still between 50 and 75 x10ˆ9/L (50 000 and 75 000 cells/mm^3^) or if the WCC is still between 2 and 3 x10ˆ9/L (2000 and 3000 cells/mm^3^), then the second ATG or placebo infusion dose will be reduced by 50%. Specifically, dose reduction will be achieved by administering 50% of the infusion volume (250 mL) instead of the full volume (500 mL). Dose reduction, and the reason, will be documented in the eCRF. Discontinuation of trial treatment (ATG/placebo) should be considered if persistent and severe thrombocytopaenia (<50 x10ˆ9/L or 50 000 cells/mm^3^ for platelets) occurs or leucopaenia (< 2 x10ˆ9/L or 2000 cells/mm^3^ for WCC count) develops on repeat FBC.

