### Intervention summary

The total dose of ≤2.5 mg/kg ATG will be split into two separate part-doses for intravenous administration over two consecutive days. On treatment day 1, the first infusion of 0.5 mg/kg or 0.1 mg/kg ATG, or placebo of the same volume, will be given over a minimum of 12 hours. On treatment day 2, the second part-dose will be infused over a minimum of 8 hours, commencing between 12 and 24 hours after the first part-dose. A maximum of 60 hours from the start of the first infusion will be allowed to complete all trial drug administration, otherwise the infusion will be discontinued, and no further trial drug will be administered. The trial pharmacist will be responsible for calculating the dose for the participants according to their weight and to the randomisation cohort the participant has been allocated to via the electronic randomisation system, as detailed in the below section ‘Randomisation and blinding’. The weight of the participant at the baseline visit will be used to calculate the dose amount which can be rounded up or down to the nearest ml. The placebo (0.9% sodium chloride solution) will be sourced from local hospital stock. There will be an identical volume of infusion solution between ATG and placebo dosages, and identical labelling will be used for the ATG infusion bag and placebo.

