### Randomisation

Prior to randomisation and treatment, the investigator or design will review baseline data to reconfirm that the participant is safe to receive trial treatment and continues to fulfil the eligibility criteria. Randomisation should be performed before the participant is due to receive their first trial treatment infusion, allowing sufficient time for treatment preparation. Randomisation should only occur for whom the eligibility criteria can be confirmed.

### Treatment day 1 and 2

Participants will be under strict medical supervision in hospital for the treatment visit. The total dose of trial treatment will be given over two consecutive days by intravenous infusion.

Treatment day 1 will be ≤6 ±3 weeks from T1D diagnosis. Changes to health and medications since the baseline visit should be checked including a SARS-CoV-2 test, and blood pressure, heart rate, oxygen saturation, respiratory rate and temperature will be recorded. The participant should also be physically examined for evidence of current infection prior to administration of premedication. It is recommended that concomitant medication with heparin and hydrocortisone, and premedication with corticosteroid, antihistamine and acetaminophen, is given as described in the MELD-ATG Pharmacy Manual, to limit ARs from peripheral ATG/placebo infusion. Blood glucose levels may be affected by premedication and will be managed by the responsible investigator.

The first part-dose of 0.5 mg/kg or 0.1 mg/kg ATG, or placebo of the same volume, will be given as an intravenous infusion over a minimum of 12 hours. AEs throughout the infusion until the end of the visit will be recorded. At the end of the infusion, blood will be collected for FBC, clotting studies (PT and APTT), if PT and/or APTT were abnormal but not beyond exclusion criteria at the screening visit, as well as renal and liver function. The FBC will be reviewed in order to confirm that it is safe to continue with the second treatment infusion.

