### Early discontinuation/withdrawal of participants

A participant may choose to not start or to discontinue trial treatment early at any time before or during trial treatment or to withdraw from future participation in the trial at any time. This may be done without necessarily giving a reason, and without any personal disadvantage and without affecting their usual clinical care. An investigator may choose to discontinue trial treatment early (eg, due to toxicities) or to stop the participation of a participant after consideration of the benefit/risk ratio. Possible reasons are: (1) continued non-compliance with the trial protocol, (2) technical grounds (eg, participant moves) and (3) early termination at the request of the CI/PI. A reason must be provided for investigator decisions.

Discontinuation of trial treatment (participant or investigator decision) does not automatically entail withdrawal from the trial. Participants who discontinue trial treatment early are expected to continue with the follow-up assessments and sample collection per protocol, as part of the intention-to-treat analysis. Discontinuation from trial follow-up visits should be the last possible solution. Participants that withdraw after randomisation will not be replaced. Trial treatment discontinuation or participant withdrawal and the reason (where available) will be documented in the eCRF. In cases of withdrawal, permission to retain samples and data already collected will be documented in the eCRF.

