### Dose delays and missed doses

Following review of the FBC obtained following completion of the first trial treatment (ATG or placebo) infusion, the dose of the second infusion may be reduced by 50% in certain scenarios.

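### The repeat blood count rule orders both a full and a halved second infusion when platelets and white cells were both low and only one recovers

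*Protocol article*

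**What the plan says.** The rule is in the Protocol article, Toxicity management, in the paragraph on haematological effects. All counts are in units of 10^9/L.

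- **Trigger.** A 50% cut in the second infusion is permissible if, after the first infusion, platelets are 50 to 75 or WCC is 2 to 3.
- **Full dose on repeat.** "Before this happens, the FBC will first be repeated and if the platelet count is over 75", or if the WCC is over 3, "then the second ATG or placebo infusion will be given as planned".
- **Half dose on repeat.** If platelets are still 50 to 75, or the WCC is still 2 to 3, "then the second ATG or placebo infusion dose will be reduced by 50" per cent. In practice 250 mL is given instead of 500 mL.
- **Stopping.** "Discontinuation of trial treatment (ATG/placebo) should be considered if persistent and severe thrombocytopaenia" (below 50) occurs, or if the WCC is below 2 on repeat.

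Three other places touch on the rule. Dose delays and missed doses says only that "the dose of the second infusion may be reduced by 50% in certain scenarios". Treatment day 1 and 2 explains the purpose of the count: "The FBC will be reviewed in order to confirm that it is safe to continue with the second treatment infusion". Early discontinuation/withdrawal of participants adds a general discretion: "An investigator may choose to discontinue trial treatment early (eg, due to toxicities) or to stop the participation of a participant". None of them ranks the full-dose order against the half-dose order.

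**The concern.** The two repeat-count sentences are meant to divide participants into those who get the full second infusion and those who get half. With 'or' in both, they overlap. A participant who qualified on both counts and recovers on only one satisfies each sentence. Each is worded as an instruction ('will'), and no order of precedence is given.

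This count is the safety check before the second infusion, in a trial that steps down to 5 years of age. In the overlap, the article does not tell the site which of two doses to prepare. Whichever dose is given follows one sentence and departs from the other, so it is also unclear what would count as a deviation under the section on protocol compliance.

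**Working it through.** The plan gives no figure to reproduce. The check enumerates the rule and adds short dose arithmetic.

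**Inputs.** The thresholds are those listed above from Toxicity management. The part-doses come from Intervention summary: "On treatment day 1, the first infusion of 0.5 mg/kg or 0.1 mg/kg ATG, or placebo of the same volume". That section does not tie either part-dose to an arm.

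**Rule as written.** P is the repeat platelet count and W the repeat WCC.

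- FULL = (P > 75) or (W > 3)
- HALF = (50 ≤ P ≤ 75) or (2 ≤ W ≤ 3)
- CONSIDER STOPPING = (P < 50) or (W < 2)

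For a participant with both counts low at first, every part of each condition applies:

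| Repeat P | Repeat W | FULL | HALF | Consider stopping | FULL if 'and' replaces 'or' |
|---|---|---|---|---|---|
| <50 | <2 | no | no | yes | no |
| <50 | 2–3 | no | yes | yes | no |
| <50 | >3 | yes | no | yes | no |
| 50–75 | <2 | no | yes | yes | no |
| 50–75 | 2–3 | no | yes | no | no |
| **50–75** | **>3** | **yes** | **yes** | no | no |
| >75 | <2 | yes | no | yes | no |
| **>75** | **2–3** | **yes** | **yes** | no | no |
| >75 | >3 | yes | no | no | yes |

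As written, 2 of the 9 combinations order both doses. Among the 4 combinations with P at least 50 and W at least 2, it is 2 of 4. With 'and' in the full-dose condition, no combination orders both, and the two conflicting rows resolve to HALF alone.

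**One count low at first.** The word 'still' in the half-dose sentence suggests that each part refers to the count that was low. On that reading, a participant with one low count gets a single instruction, and 0 of the 4 combinations with P at least 50 and W at least 2 conflict.

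**Dose at stake, 2.5 mg/kg arm.** Full total = 2.5. Halved total = day 1 part-dose + (2.5 − day 1 part-dose) / 2.

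- Day 1 = 0.5: second infusion 2.0, halved 1.0, total 0.5 + 1.0 = 1.5 mg/kg. Reduction 1.0 / 2.5 = 40%.
- Day 1 = 0.1: second infusion 2.4, halved 1.2, total 0.1 + 1.2 = 1.3 mg/kg. Reduction 1.2 / 2.5 = 48%.

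**The case against.** The best defence is that the intent is plain. The reduction is triggered by either count, the repeat asks whether the problem has resolved, and the later sentence halves the dose if either count is still low. Read in sequence and for its safety purpose, persistence of either count means halving. That is probably what was meant, and it is why the repair is small. It does not remove the conflict, because the full-dose sentence says the opposite for the same participant and is just as firm.

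A second defence is that the section offers guidance only. It opens by saying that the guidance may be followed for toxicity reactions, and names haematological effects among them. But that sentence concerns reactions during the infusion and covers interruption and discontinuation. The count here is taken after the infusion, and the question is a dose reduction. Investigator discretion to stop treatment does stand, so a reader who infers that anyone must be given a full dose goes beyond the text.

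A third defence is that the product label, the Trial Manual or the full protocol may settle the matter. They are not shown, so it cannot be claimed that sites will in fact differ. The point is limited to the algorithm printed in the article, which gives thresholds, actions and volumes and contradicts itself.

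The case is also narrow, and this objection stands in full. It needs both counts in their low bands after the day 1 part-dose alone, in participants screened to exclude clinically significant leucopaenia and thrombocytopaenia, and then exactly one recovery. The paragraph does foresee the two effects occurring together, but gives no rate.

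**Conclusion.** The point holds. For a participant with both counts low at first, one recovered and the other still in its low band, the article orders the second infusion both as planned and halved, with no tie-break. The case is narrow and its frequency is unknown: 2 of 9 counts table cells, not participants. No sample size, power, error rate or analysis is affected.

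Three stronger readings are tempting and not supported:

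- **That a participant with one persistently low count is caught too.** This follows only from the most literal reading, in which the count that was normal throughout also triggers the full dose. The word 'still' points the other way.
- **That the conflict moves participants in the 2.5 mg/kg arm onto the 1.5 mg/kg arm's dose.** The totals coincide only if day 1 is 0.5 mg/kg. If it is 0.1 mg/kg, the halved total is 1.3. Any valid halving has the same effect on total dose; the ambiguity adds only that the text does not say which total applies.
- **That the article implies a 50% ceiling when a repeat count falls below 50 or 2.** It says only that discontinuation should be considered. A ceiling would be a new clinical rule with no basis in the document.

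**What to change.** In the full-dose sentence of the haematological paragraph, replace 'or' with 'and': the second infusion is given as planned only if platelets are over 75 x10^9/L and WCC is over 3 x10^9/L on repeat. Keep 'or' in the half-dose sentence. Leave the discontinuation sentence unchanged and add no dose ceiling.

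The cost is a one-word protocol clarification and a memo to sites. Sample size, visits and analysis stay as they are. If the Trial Manual or the full protocol already has the 'and' wording, it is enough to confirm that and align the text.

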### Infusion site management

Infusion site reactions are relatively common with both IMP and placebo but can be minimised by application of a cold pack to the infusion site 2–3 min before and immediately after the infusion to reduce the associated discomfort.

### Statistics overview

The trial design consists of seven cohorts, each recruited sequentially, with between three and five treatment arms (there will be fewer arms for later cohorts). The total sample size is 114 participants allocated to treatment arms. The primary endpoint of interest is the area under the C-peptide curve (AUC) over the first 2 hours (using all available time points) obtained after an MMTT (AUC C-peptide) at 12 months follow-up; it will be undergo the transformation ln(x+1) for the primary analyses.

All model assumptions will be checked via graphical means such as plotting residuals versus dose and fitted values. We will transform our primary outcome, MMTT AUC C-peptide value to ln(AUC C-peptide +1). The transformed MMTT AUC C-peptide value is assumed to be normally distributed; this distributional assumption will be assessed using a Q-Q plot and whether the residuals of the model deviate from a straight line. If the residuals are not normally distributed, then the outcome will be transformed to improve this assumption. If no transformation is available, then non-parametric methods will be used.

